#### Safety measures

Self-reported anxiety and depression symptoms are measured by the BAI and BDI-II. Suicidal ideation is evaluated in the MINI interview. Data on death are obtained from the Danish Cause of Death Register [45]. The number of outpatient services, admissions, inpatient days, and life-threatening conditions for reasons other than suicide attempts are obtained from the Danish National Patient Registry (Landspatientregistret) [3] containing data on Danish patients’ contacts with hospitals in Denmark. Numbers of sick leave days are obtained from the DREAM database.

#### Outcome measures in the detection of depression study

The primary outcome for the detection of depression study is the positive predictive value of referral diagnosis in two randomised detection settings: case-finding and standard detection. In the standard detection group, based on results from the referral diagnosis performed by the GP and the MINI carried out by the research assistant, the positive predictive value of the GP’s diagnosis is calculated. In the case-finding group, based on results from the MDI and MINI, the positive predictive value of the diagnosis and the sensitivity, specificit, and negative predictive value of the diagnosis are calculated.

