### The detection of depression study

Bower et al. reports that systematic identification of patients is an “active ingredient” in CC [11], so we want to include systematic identification in the Collabri depression study, and to use a method that can be carried out by GPs. Studies indicate that GPs fail to diagnose about half of patients with depression in general practice [12, 13]. There is substantial evidence that routine screening will lead to too many false positives [12], because of the modest prevalence of depression in primary care. However, the US Preventive Task Force reports evidence supporting screening for depression [14]. One factor for the opposing conclusions is that the latter includes research where screening is supported by subsequent treatment [15].

To sum up, screening for depression is recommended in the USA, but not in the UK and in Denmark, where screening is only recommended in high-risk groups [1]. Nevertheless, screening of high-risk groups is not supported by subsequent literature. A randomised controlled trial on high-risk screening found no difference in recognition rates between the intervention group and the control group [16]. In a prospective cohort study, as a final result of screening, only 1% (17/1687) started treatment for major depressive disorder [17]. Finally, in a Danish observational study investigating high-risk screening for depression with the Major Depression Inventory (MDI), compared with screening with MDI on clinical suspicion (called case-finding) and a combination of the two methods, investigators found that screening of patients in high-risk groups had limited effect in addition to the cheaper and less invasive method of case-finding [18].

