#### Individual level

Patients are eligible for the outcome study and the detection of depression study if their GP participates in the study and the patient complies with the following inclusion and exclusion criteria, assessed either by the GP at recruitment and/or by a research assistant at a baseline eligibility interview. Patients are eligible for the outcome study if they are diagnosed with depression according to the ICD-10. Patients are eligible for the detection of depression study if they are referred to the study either by their GP in the standard detection group with a depression diagnosis or by their GP in the case-finding group with a (positive or negative) MDI score. In both studies, patients must be 18 years of age, Danish speaking and give her/his written informed consent to participate in the trial on the terms described.

Patients cannot participate in the Collabri studies and are excluded at baseline if they have a high risk of suicide, a current psychotic condition, obsessive compulsory disorder (OCD), post-traumatic stress disorder (PTSD), bipolar affective disorder, or alcohol or substance misuse that prevents the person from participating in the Collabri intervention. Patients are also excluded at baseline if they are in current therapeutic or medical treatment for anxiety or depression, have a pending disability pension case, or have been treated for anxiety or depression within the last 6 months. Additionally, patients diagnosed with dementia and patients assessed by the GP to be medically unstable, making it impossible to adhere to treatment, cannot participate. Further, patients cannot participate if they are referred to treatment in the secondary psychiatric caresystem not later than at first contact with the GP after inclusion by a research assistant is referred to treatment in the secondary psychiatric care system. Patients in the intervention group are excluded if they want treatment cf. the psychologist scheme and do not want referral to the psychologist to be preceded by treatment according to the Collabri model.

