The results of this trial will add to the knowledge of collaborative care for depression in a Scandinavian context. If the Collabri model is shown to be more effective than treatment as usual in general practice, the results can contribute to improving the care and treatment for patients with depression in general practice with benefits to both patients and society. The results of the detection of depression study add to the knowledge of detection of depression in primary care. If case-finding is shown to be superior to standard detection, it will be recommended as a detection method in future treatment according to the Collabri model.

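### The detection study labels its primary outcome as the PPV of the referral diagnosis but computes it from the GP's diagnosis in one arm and the MDI in the other; a PPV difference alone cannot show better detection

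*Protocol article*

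**What the plan says.** The section on outcome measures in the detection study opens with a single outcome for both arms: "The primary outcome for the detection of depression study is the positive predictive value of referral diagnosis in two randomised detection settings". It then gives two calculations. Under standard detection, "based on results from the referral diagnosis performed by the GP and the MINI carried out by the research assistant", it says that "the positive predictive value of the GP’s diagnosis is calculated". Under case-finding the inputs change: "In the case-finding group, based on results from the MDI and MINI, the positive predictive value of the diagnosis". Sensitivity, specificity and negative predictive value (NPV) are planned for case-finding only.

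Entry to the study differs in the same way (Eligibility, Individual level). Standard-arm patients are "referred to the study either by their GP in the standard detection group with a depression diagnosis", while case-finding patients come in "by their GP in the case-finding group with a (positive or negative) MDI score". Under Recruitment and randomisation (Cluster level), standard-arm GPs use the MDI as often as they normally would, and case-finding GPs use it systematically once they suspect depression.

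The Statistical analysis section names only PPV for comparison between the detection arms. The Abstract asks whether case-finding is the better way of detecting depression. The Background gives the motivation: "Studies indicate that GPs fail to diagnose about half of patients with depression in general practice". The Discussion states the consequence: "If case-finding is shown to be superior to standard detection, it will be recommended as a detection method", with the sentence going on to confine this to later use of the Collabri model. The Abstract says the same.

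**The concern.** There are two linked problems.

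First, the label and the calculation disagree in the case-finding arm. An MDI result in a suspected patient is not the GP's referral diagnosis, and the protocol treats the two as separate items: the Blinding section withholds both from the interviewer. It does not say what counts as a positive referral diagnosis under case-finding. A PPV difference may therefore mix the effect of the randomised detection method with a switch of index result.

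Second, PPV is the share of positives that are true. It says nothing about depressed patients who were never flagged. The standard arm refers only positives, so sensitivity and NPV cannot be estimated there and cannot be compared between arms. Under case-finding they apply only to patients whom the GP already suspected. No between-arm measure named in the protocol counts cases found.

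At stake is the wording of the detection study's conclusion and the recommendation attached to it. The treatment trial's primary outcome is not affected.

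**Working it through.** **1. The plan's own figure.** Inputs: PPV 45% and 60%, power 0.8, significance level 0.05 (Sample size calculation for the detection study); 48 GPs with 10–11 patients each (Feasibility); ICC 0.04 (stated for the treatment outcome, assumed here to apply to PPV too). A two-sided test is assumed.

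n per arm = [1.96·√(2·0.525·0.475) + 0.8416·√(0.45·0.55 + 0.60·0.40)]² / 0.15² = 173, or 346 in total.

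Design effect = 1 + (m − 1)·0.04:
- m = 10: 346 × 1.36 = 470.6
- m = 10.5: 346 × 1.38 = 477.5
- m = 11: 346 × 1.40 = 484.4

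The stated 480 is reproduced to within 3%. The study is sized as a comparison of two PPVs, and the arithmetic is not at issue. The same section refers to the 60% as a level of detection, which blurs PPV with cases found.

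**2. What PPV fixes and what it leaves open.** PPV = TP/(TP + FP), so FP = TP·(1 − PPV)/PPV. PPV fixes only the ratio of false to true positives; the number of true positives is free.

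**3. Illustrations at the planned effect.** The suspected pools and the MDI sensitivities are assumptions and are not in the documents. Specificity is solved so that PPV is exactly 60%. Reference: standard detection diagnoses 20 patients, of whom 20 × 0.45 = 9 are depressed.

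| MDI applied to | Sensitivity | TP | FP = TP × 0.40/0.60 | Specificity | Cases against 9 |
|---|---|---|---|---|---|
| the same 20 (9 depressed, 11 not) | 0.80 | 7.2 | 4.8 | 1 − 4.8/11 = 0.56 | 20% fewer |
| the same 20 | 0.90 | 8.1 | 5.4 | 1 − 5.4/11 = 0.51 | 10% fewer |
| a wider 30 (12 depressed, 18 not) | 0.75 | 9.0 | 6.0 | 1 − 6.0/18 = 0.67 | equal |
| a wider 30 | 0.80 | 9.6 | 6.4 | 1 − 6.4/18 = 0.64 | 0.6/9 = 7% more |

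Every row delivers the full planned PPV gain. The direction of the change in cases found depends on inputs that PPV does not show.

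**4. Effect of switching the index result.** Take the wider pool of 30 again. Suppose that case-finding GPs still diagnosed the same 20 patients, 9 of them correctly. The PPV of the referral diagnosis would be 45% in both arms. Scored on the MDI as in the last row, the same case-finding patients give 9.6/16 = 60%. Under these assumptions the whole planned difference arises from the choice of index result. This shows what is possible and is not an estimate.

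**The case against.** Different positives in the two arms are partly inherent in the design. Practices are randomised to a detection method, and a comparison of two strategies may legitimately score each on its own positive result. That stands: a reader might infer that the differing index results make the comparison invalid, and the documents do not support going so far. What remains is that the outcome is named as something else, and that a positive is left undefined for case-finding.

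PPV is also relevant to the plan's rationale. The Background worries about false positives from routine screening as well as about missed cases, and the recommendation concerns entry to the Collabri programme, where the correctness of positives matters. That stands too. PPV is pertinent but not sufficient for a claim about detection. The recommendation sentences do not name PPV as the trigger; this is inferred from its being the primary outcome and the only between-arm measure named.

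A reader might further infer that case-finding would lose 10–20% of true cases. The arithmetic behind those figures is correct, but it reuses the 45% PPV as the prevalence in a fixed pool of suspected patients, so the MDI can only remove cases. GPs may suspect more patients than they diagnose, and the protocol itself foresees referred patients whom the GP had not diagnosed but the MINI finds depressed. With a wider pool the sign can reverse.

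Further secondary comparisons may sit in an analysis plan that is not shown. That would not remove the conflict within the outcome definition.

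**Conclusion.** The point holds in this form. The primary outcome's label and its calculation disagree in the case-finding arm and must be reconciled. A higher PPV is compatible with more, equal or fewer true cases found, so it cannot by itself support a claim of better detection or the recommendation in the Abstract and Discussion.

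This conclusion needs no assumption about MDI accuracy; it follows from the definition of PPV and from the standard arm referring only positives. The size of any gain or loss in cases cannot be derived from the documents. The illustrated range, 20% fewer to 7% more at the same 60% PPV, depends entirely on the assumed sensitivities and pools.

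**What to change.** 1. Define one referral-positive rule for the primary comparison, preferably the GP's referral diagnosis of depression against the blinded MINI in both arms. The baseline interview section and Table 1 list a referral diagnosis from the GP without limit by arm, but do not confirm that one exists for MDI-negative patients referred to the detection study only, so check this first. Where it was not recorded, say so. If MDI positivity has to stand as the case-finding result, rename the outcome and define a positive in each arm.
2. Report the MDI's PPV, sensitivity, specificity and NPV as secondary results within case-finding, valid only among GP-suspected patients.
3. Add a supportive randomised comparison of MINI-confirmed depression cases per practice, accounting for the number of GPs under each provider number and for recruitment time. Practice list sizes are not stated as collected. State that the count also reflects recruitment effort and consent, and that no margin or power has been set for it.
4. Limit a PPV-only result to the accuracy of positive referrals. Do not word it as better detection unless the comparison of confirmed cases is reported beside it and does not point the other way.

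The cost is revised outcome wording, one extra count analysis and a more cautious conclusion. No new patients are needed.

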### Recruitment and randomisation

#### Cluster level

Recruitment of GPs ran from May 2014 to July 2015. GPs in the catchment areas of the Capital Region in Denmark were invited to join the study through letters with information about the project and dates for a total of four information meetings. Additionally, the GPs were recruited through articles in professional newsletters and forums. Information visits and telephone calls to GPs were made on request.

The randomisation was conducted by centralised random computer-generated allocation sequence, carried out externally by the Research Centre for Prevention and Health (RCPH) at practice level, where each cluster corresponds to a provider number consisting of one or more GPs. Cluster randomisation was chosen because of the risk of bias in the form of contamination if the randomisation was on an individual level. The GPs were randomised to give either treatment as usual or CC according to the Collabri model. In both the treatment as usual group and the CC group, the GPs were subsequently randomised according to detection method, which was either standard detection of depression or case-finding. In standard detection the GPs were asked to use the MDI [19] as often as they usually did. In case-finding the GPs were asked to systematically use the MDI as a screening tool if they suspected depression. See Fig. 1 for an illustration of the randomisation process.

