#### Individual level

Patients within the clusters are allocated to the same group as their GP. The GPs enrolled in the study detect patients with depression according to randomisation allocation. Only patients who meet the criteria for depression at baseline are included in the depression study. Patients who have not initially been diagnosed with depression by the GP and have only been referred to the detection of depression study, and are subsequently diagnosed with depression through the Mini International Neuropsychiatric Interview (MINI), are asked to participate in the treatment outcome study if the GP agrees with the diagnosis.

The GP obtains verbal consent from the patient that a research assistant can make contact by telephone in order to conduct a diagnostic interview (MINI interview). If the diagnosis according to the MINI interview is inconsistent with the GP’s diagnosis, the research assistant consults a psychiatrist in the Collabri group, who contacts the GP to confirm which diagnosis is correct. Patient recruitment was initiated in November 2014 and ended on 31 December 2016.

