### Blinding

It is not possible to ensure blinding of the patient and GP, but the blinding of GP allocation to intervention group is maintained for researchers in the data collection phase and in the analysis phase. The intervention groups are coded and anonymised (e.g. X and Y) so that researchers are blinded in the entire phase of the analysis and when writing the conclusion. In the detection of depression study, blinding of the patient diagnosis and the MDI result is maintained for the researchers during the MINI interview, in order to ensure that the evaluation of diagnosis is not affected by the GP’s referral diagnosis.

Care managers, GPs, psychiatrists, and patients are notified that they cannot reveal to the researchers to which group the patients are allocated. If the blinding is broken and referral diagnosis, or baseline or outcome measures are revealed at the baseline interview or at the follow-up interview, the patient is referred to another blinded researcher.

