## Discussion

The Collabri model is based on the evidence supporting CC in other countries. To our knowledge this is the first randomised trial investigating the effect of a CC model for depression in a Scandinavian context. The strength of the outcome study is the centralised computer-based cluster randomization, which ensures adequate generation of the allocation sequence and adequate allocation concealment. The use of blinded outcome assessors for the secondary outcome, the fact that it is a register-based outcome, and the use of intention-to-treat analysis decreases the risk of biased effect estimates. The strength of the detection of depression study is also the centralised computer-based cluster randomisation and the use of blinded assessors of the outcomes. The trial is registered at http://www.clinicaltrials.gov, which helps prevent selective and incomplete outcome reporting. The fact that we monitor fidelity to the Collabri model after 6 months is also a strength of the trial. This is intended to ensure that care managers, psychiatrists, and GPs are true to the model. A limitation of this trial is that we are not able to blind participants, care managers, psychiatrists, or GPs to the allocation. Another limitation is that the primary outcome is self-reported and therefore not blinded, which may well lead to overestimation of treatment effects. Some might argue that it is difficult to sustain the blinding of the assessor during follow up, and this certainly leads to risk of bias. Should blinding be broken, a second assessor will complete the follow-up interview.

Although participants are recruited from general practices throughout the Capital Region of Denmark, and should be fairly representative of the population in the region, there may be reduced external validity. As it is the GP who identifies eligible participants, not everybody with depression who is eligible may be asked to participate, as patients are not systematically screened for eligibility. Due to differences in healthcare systems, the results may not be directly comparable with other countries, but together with other trials in the area, it will give a more complete picture of the effects of collaborative care in people with depression.

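### Sensitivity and specificity of case-finding rest on GP-referred patients only, with no stated rule that makes referral independent of the MDI result

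*Protocol article*

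**What the plan says.** The section on outcome measures in the detection study makes PPV the primary outcome. For standard detection it plans PPV alone. For the other arm it goes further: "In the case-finding group, based on results from the MDI and MINI", it says that "the positive predictive value of the diagnosis and the sensitivity, specificit, and negative predictive value of the diagnosis are calculated".

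Four other statements determine who can appear in that MDI-by-MINI table:

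- Recruitment and randomisation, cluster level: "In case-finding the GPs were asked to systematically use the MDI as a screening tool if they suspected depression". The MDI is thus given on suspicion, not to every attender.
- Eligibility, individual level: patients enter if referred "by their GP in the case-finding group with a (positive or negative) MDI score". MDI-negative patients are expressly admitted.
- Recruitment and randomisation, individual level: there is a route for "Patients who have not initially been diagnosed with depression by the GP and have only been referred to the detection of depression study". If the MINI then shows depression and the GP agrees, they are invited into the treatment study.
- Same section: "The GP obtains verbal consent from the patient that a research assistant can make contact by telephone". The MINI follows only after that.

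The Blinding section adds that "blinding of the patient diagnosis and the MDI result is maintained for the researchers during the MINI interview". This protects the reading of the MINI but has no bearing on who receives one.

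**The concern.** Sensitivity and specificity can be read directly from a test-by-reference table only if the chance of receiving the reference standard does not depend on the test result, or on true status given that result. Here GPs are asked to use the MDI systematically once they suspect depression, but no stated rule asks them to refer systematically everyone who completed one. The table therefore contains referred, consenting patients, not all tested patients.

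Unequal referral is plausible. The Feasibility section sets each GP's target in people with depression (10-11 each). A patient diagnosed with depression has a direct route to the treatment study, whereas an undiagnosed patient reaches it only through a positive MINI and the GP's agreement.

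At stake is how the accuracy figures will be read. The Background motivates the detection study by reporting that GPs fail to diagnose about half of patients with depression, so readers will look for sensitivity. An inflated figure would suggest that case-finding misses fewer patients than it does.

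**Working it through.** **The plan's own figure.** For PPV 45% versus 60%, two-sided 5% and 80% power:

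n per arm = [1.96 × √(2 × 0.525 × 0.475) + 0.842 × √(0.45 × 0.55 + 0.60 × 0.40)]² / 0.15² = 173 after rounding up, so 346 in total.

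The design effect is 1 + (m − 1) × 0.04. The ICC of 0.04 is given for the treatment study, and its use here is an assumption. For m = 10, 10.5 and 11 the totals are 346 × 1.36 = 471, 346 × 1.38 = 477 and 346 × 1.40 = 484. The stated 480 is reproduced. Sensitivity and specificity do not enter it.

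**Referral depends on the MDI result only.** The documents give no true sensitivity (Se), specificity (Sp) or verification fractions, so all inputs are assumptions: Se = 0.85, Sp = 0.75, fraction of MDI-positives verified vp = 0.9, fraction of MDI-negatives verified vn varied.

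Apparent Se = Se·vp / [Se·vp + (1 − Se)·vn]

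Apparent Sp = Sp·vn / [Sp·vn + (1 − Sp)·vp]

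| vn | Apparent Se | Apparent Sp |
|---|---|---|
| 0.9 | 0.765/0.900 = 0.850 | 0.675/0.900 = 0.750 |
| 0.7 | 0.765/0.870 = 0.879 | 0.525/0.750 = 0.700 |
| 0.5 | 0.765/0.840 = 0.911 | 0.375/0.600 = 0.625 |
| 0.3 | 0.765/0.810 = 0.944 | 0.225/0.450 = 0.500 |
| 0.2 | 0.765/0.795 = 0.962 | 0.150/0.375 = 0.400 |

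The first row is equal referral, with no bias. At vn = 0.5 the apparent share of missed cases is 9%, against a true 15%. PPV and NPV stay correct in every row, because each is computed within one MDI result.

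**Referral of negatives also depends on true status.** Assume prevalence 0.45 among tested patients (illustrative), Se = Sp = 0.80, and referral of 70% of MDI-positives, 90% of depressed MDI-negatives and 30% of non-depressed MDI-negatives. As shares of tested patients:

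- true positives 0.45 × 0.80 × 0.7 = 0.252
- false negatives 0.45 × 0.20 × 0.9 = 0.081
- false positives 0.55 × 0.20 × 0.7 = 0.077
- true negatives 0.55 × 0.80 × 0.3 = 0.132

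Apparent Se = 0.252/0.333 = 0.76 (true 0.80). Apparent Sp = 0.132/0.209 = 0.63 (true 0.80). Apparent NPV = 0.132/0.213 = 0.62, against a true 0.44/0.53 = 0.83. PPV = 0.252/0.329 = 0.77, unchanged from 0.36/0.47.

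In general, apparent sensitivity is too high when depressed MDI-negatives are referred less often than depressed MDI-positives, and too low when they are referred more often.

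**What a Begg-Greenes correction does in each case.** It weights PPV and NPV from verified patients by the shares of positive and negative MDIs among all tested:

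Corrected Se = PPV·P(+) / [PPV·P(+) + (1 − NPV)·P(−)]

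In the first case PPV and NPV are correct, so the true 0.85 and 0.75 are recovered. In the second, P(+) = 0.36 + 0.11 = 0.47 and P(−) = 0.53. Corrected Se = 0.36 / [0.36 + (0.081/0.213) × 0.53] = 0.36/0.56 = 0.64, further from 0.80 than the uncorrected 0.76. The correction is only as good as its assumption that referral is unrelated to true status given the MDI result.

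**The case against.** The strongest reply is that the plan intends MDI-negatives to be verified. Eligibility names them, and the recruitment section gives undiagnosed patients a route to the MINI and, if depressed, to the treatment study. A reader might infer that such patients have little reason to be referred and that sensitivity will therefore be overstated. The documents do not support that. They give no referral fractions, equal referral gives no bias, and referral driven by remaining suspicion can reverse the direction for sensitivity. This part of the reply stands. What it does not show is that verification is complete or unrelated to the MDI result, since admitting negatives is not the same as requiring them.

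A reader might also take the Discussion as conceding the mechanism, because it says that "not everybody with depression who is eligible may be asked to participate, as patients are not systematically screened for eligibility". That sentence is about external validity and does not mention referral differing by MDI result.

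Nor do these measures threaten the recommendation of case-finding. That is conditional on superiority over standard detection, while sensitivity is calculated in one arm only and the between-arm comparison is of PPV. Because the MDI is used only on suspicion, even a fully verified sensitivity would say nothing about patients whom GPs never suspect.

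Finally, a fuller protocol or SAP, not shown, may contain a referral log or a correction. The article does not exclude one. The point is therefore about what the stated calculation can support on the data as described, not about a missing detail.

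**Conclusion.** The concern holds in conditional form. The case-finding sensitivity and specificity are open to partial verification bias, because the MINI reaches only GP-referred, consenting patients and no stated rule requires all or consecutive MDI-tested patients to be referred. If negatives are referred less often than positives, regardless of true status, sensitivity is too high and specificity too low. Under the assumed 85%/75%, with 90% of positives verified, apparent values run from 88%/70% when 70% of negatives are verified to 96%/40% when 20% are. If GPs refer mainly negatives they still suspect, sensitivity may instead be understated, and NPV is biased as well. Neither size nor direction can be settled from the documents.

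The damage is confined to additional measures in one arm. Under-referral of negatives leaves the primary PPV comparison, the sample size of 480 and the superiority condition for recommending case-finding untouched.

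**What to change.** Amend the paragraph on outcome measures in the detection study as follows.

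1. Where counts of completed MDIs, positive and negative, can be obtained from practice records, estimate sensitivity and specificity with a Begg-Greenes correction. State its assumption that, given the MDI result, referral is unrelated to true status. Show a range over referral fractions, including fractions that differ between depressed and non-depressed MDI-negatives.
2. Where counts cannot be obtained, report PPV and NPV only, noting that NPV rests on the same assumption. Alternatively, label sensitivity and specificity as applying to GP-suspected, referred patients and not as the share of depression detected.

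A new prospective tally by GPs is no longer possible, since patient recruitment ended on 31 December 2016. The first option costs a search of practice records and a standard formula; the second costs only wording. The downside is wider confidence intervals and a less favourable, or absent, sensitivity figure.
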